# Effect of Kami Guibi-tang (KGT) in elderly subjects with insomnia: a study protocol from a single center, randomized, double-blind, placebo-controlled trial

**DOI:** 10.1186/s12906-023-04199-y

**Published:** 2023-10-23

**Keywords:** Insomnia, Subjective cognitive decline, Kami Guibi-tang, Herbal medicine, Randomized controlled trial, Protocol

## Abstract

**Background:**

The incidence of insomnia increases with age and is related to cognitive function in older adults; therefore, it is important to manage it actively. In this study, we report a protocol for the evaluation of the efficacy and safety of Kami Guibi-tang (KGT), a herbal prescription that has been widely used in East Asia for insomnia, forgetfulness, and depression, in older adults with insomnia.

**Methods:**

In this single-center, double-blind, randomized controlled trial, 60 older adults with insomnia and subjective cognitive decline will be recruited and randomly assigned to the KGT or placebo group. The KGT group will take KGT granules thrice a day for 12 weeks, whereas the control group will take placebo granules in the same manner.

Participants will be assessed for sleep, cognitive function, quality of life, and depression using the Pittsburgh Sleep Quality Index-Korean (PSQI-K), Insomnia Severity Index-Korean (ISI-K), Seoul Neuropsychological Screening Battery–Dement (SNSB-D), 36-item MOS Short Form Survey (SF-36) and Short version of the Geriatric Depression Scale (S-GDS) before and at the end of administration of the investigational product. The PSQI-K, ISI-K, and SF-36 will be further assessed 12 weeks after the end of medication to determine whether the effects on sleep and quality of life are sustained. The PSQI-K total score difference between the two groups at 12 and 24 weeks will be the primary outcome; all other endpoints will be secondary.

Safety will be assessed by performing blood tests and electrocardiograms before taking the investigational drug, 6 weeks after taking the drug, and 12 weeks after taking the drug; any adverse events will be observed throughout the study.

**Discussion:**

The protocol will provide a detailed process for a clinical trial to evaluate the efficacy and safety of KGT in elderly patients with insomnia. We will also investigate if changes in cognitive function correlated with improvements in insomnia.

**Trial registration:**

This trial was registered at CRIS (Clinical Research Information Service) on April 27, 2023 (KCT0008391, version 2.0). https://cris.nih.go.kr/cris/search/detailSearch.do?seq=24811&search_page=L.

**Supplementary Information:**

The online version contains supplementary material available at 10.1186/s12906-023-04199-y.

## Background

Insomnia disorder is characterized by complaints of one or more of the following symptoms: difficulty initiating sleep, difficulty maintaining sleep, or early morning awakening with an inability to return to sleep, at least 3 nights per week for at least 3 months by the Diagnostic and Statistical Manual of Mental Disorders, Fifth Edition (DSM-5) [1]. Insomnia is a common symptom observed in clinical practice, and approximately 30–50% of the total population experiences intermittent short-term insomnia [2]. Insomnia is more commonly observed in women than in men and increases with age [3]. Sleep deprivation is a risk factor for cardiovascular diseases, including myocardial infarction, coronary artery disease, heart failure, and stroke, and is estimated to increase cardiovascular mortality [4–6]. Additionally, insomnia has been associated with neurocognitive function [7], processing speed, attention conversion, and short-term visual memory deterioration when sleep time is short [8].

In clinical practice, sleeping pills are often initially prescribed for insomnia, and while they relieve patients’ sleep deprivation effectively in a short period, they can also cause problems of abuse and dependence [9]. In some patients, the use of sleeping pills is accompanied by adverse effects, withdrawal symptoms, and rebound insomnia. Moreover, the effects of long-term use may not be clear, as the risk of side effects increases [10]. Particularly, when elderly patients use sleeping pills for a long time, side effects such as cognitive impairment, daytime fatigue, and increased risk of falls have been reported [11].

While insomnia can cause cognitive decline [12], frequent use of sleep medication is also associated with an increased risk of dementia in some older adults [13, 14]. Therefore, in addition to conventional treatments, it is necessary to develop other effective and safe treatments for long-term use in elderly patients with insomnia. Herbal medicines that use natural products should be considered.

Kami guibi-tang (KGT; Kami-guibi-tang in Korean, Jia-wei-gui-pi-tang in Chinese, and Kami-kihi-to in Japanese) is a herbal medicine widely used for insomnia, cognitive decline, and depression [15]. KGT improved sleep defects in Parkinson’s disease models [16]. In clinical studies, it has been reported to be effective in preventing sleep deepening in patients with menopausal symptoms after treatment for gynecological malignancy [17] and in patients with cancer-related sleep disturbance [18]. Additionally, the mechanisms and effects related on cognitive function have been reported in vivo and in clinical studies [19–22].

However, few clinical studies have reported on the efficacy and safety of KGT in elderly patients with insomnia. In particular, since it has already been shown that insomnia and cognitive decline are related, there is a need to observe both symptoms in the elderly [23]. The primary aim of this clinical trial is to confirm the efficacy and safety of KGT in elderly patients with insomnia. Second, we aimed to explore whether KGT was effective in improving subjective cognitive decline in elderly individuals.

## Methods and analysis

### Study design

 This single-center, randomized, double-blind, placebo-controlled clinical trial aims to analyze the efficacy and safety of KGT granules in elderly patients with insomnia. Participants with insomnia will be administered KGT or placebo granules, one pack at a time, three times a day for 12 weeks. The effect of insomnia improvement will be evaluated using the Pittsburgh Sleep Quality Index-Korean (PSQI-K) [24] and the Insomnia Severity Index-Korean (ISI-K). The primary efficacy endpoint is the PSQI-K score, and we will assess the change in the total score at baseline, after 12-weeks and then 12 weeks after the end of the dosing period. The ISI-K will be evaluated with the same time as PSQI-K. We will evaluate changes in cognitive function using the Seoul Neuropsychological Screening Battery (SNSB) [25, 26], quality of life using the 36-item MOS Short Form Survey (SF-36) [27], and depression using the Korean version of the Short-Form Geriatric Depression Scale (SGDS-K) [28]. The enrolment, interventions, and assessments of the study are summarized in Table 1. A schematic of the study process is shown in Fig. 1. This protocol was reported in accordance with the Standard Protocol Items: Recommendations for Interventional Trials (SPIRIT) guidelines (Additional file 1).

**Table 1 Tab1:**
[figure not shown]
The schedule of enrolment, interventions, and assessments

Laboratory test (basic): AST, ALT, glucose, BUN, creatinine, Na, K, Cl, LDH, CPK

Laboratory test (add): Cholesterol, HDL-cholesterol, LDL-cholesterol, triglyceride, homocysteine, T3, free T4, TSH

ECG: electrocardiogram

*ISI-K* Insomnia Severity Index-Korean, *SCD-Q* Subjective Cognitive Decline Questionnaire, *KDSQ-C* Korean Dementia Screening Questionnaire-Cognition, *SNSB-D* Seoul Neuropsychological Screening Battery-Dementia version, S-GDS = Korean version of Short form Geriatric Depression Scale, *PSQI-K* Pittsburgh Sleep Quality Index-Korean, *SF-36* 36-item MOS Short Form Survey

**Fig. 1 Fig1:**
[figure not shown]
Flowchart of the study process

### Study setting

The Kyung Hee University Hospital at Gangdong, Seoul, the Republic of Korea, is the site of the study. Recruitment will be conducted from May 2023 to October 2024 through hospital bulletin boards, newspapers, and online advertisements.

### Eligibility

#### Inclusion criteria

Participants who meet all the criteria below are eligible to participate:Those who complain of insomnia according to the criteria presented by DSM-5 > 65 years.Those with an Insomnia Severity Index Korean (ISI-K) score of > 8.Those with a Subjective Cognitive Decline Questionnaire (SCD-Q) score of > 7 and a Korean Dementia Screening Questionnaire-Cognition (KDSQ-C) score of < 6.Those who have not received any new treatments related to insomnia within the last 2 weeks: pharmacological and non-pharmacological treatments.Those who have not received cognitive-related drug treatments within the last 2 weeks.Cognitive-related drugs include cerebral function-improving agents, cerebral circulation-activating drugs, and other drugs or nutrients that can affect cognition.Those who have been in a stable state without any change in medications for underlying diseases for the past 4 weeks or more and who are planning to take stable medications during the study period.Those who have no problems with communication.Those who voluntarily decided to participate and signed the written consent form.

#### Exclusion criteria

The exclusion criteria are as follows:

Diagnosis of dementia according to the criteria of the National Institute of Neurological and Communicative Disorders and Stroke and Alzheimer’s Disease and Related Disorders Association (NINCDS-ADRDA) [29].Diagnosed with mild cognitive impairment according to the diagnostic criteria for mild cognitive impairment suggested by Albert et al. [30]Patients with a brain disease that causes other neurological symptoms.Patients with a mental disorder, a behavioral problem requiring psychotropic drug treatment, or those who are taking a psychotropic drug.Patients with substance abuse (drug addiction, alcoholism, etc.)Patients with a physical disability that threatens life and requires immediate treatment.Uncontrolled hypertension patient.Patients with heart or kidney disease requiring acute treatment.Patients with edema.Gastrointestinal symptoms (anorexia, stomach discomfort, nausea, abdominal pain, and diarrhea).Those who are taking drugs that may cause hypokalemia or myopathy.Patient with hypersensitivity to the components of investigational drug.Clinically significant abnormalities in blood chemistry tests (AST/ALT: more than 2 times the upper limit of normal; serum creatinine: more than 10% of the upper limit of normal).Patient who participated in another clinical study and received intervention within 4 weeks.Illiteracy.Others determined by the researcher to be inappropriate.

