### Safety assessments and monitoring

Adverse events will be investigated during each visit. Subjects who took the investigational drug at least once are eligible for safety analysis. Any undesirable medical findings indicating symptoms not observed prior to the study are considered adverse events.

At every visit, blood pressure, pulse rate, and body temperature are investigated to determine the participants’ health status. Laboratory tests for glucose, aspartate aminotransferase (AST), alanine aminotransferase (ALT), blood urea nitrogen (BUN), creatinine, sodium, potassium, chloride, lactate dehydrogenase (LDH), creatine phosphokinase (CPK), and electrocardiography (ECG) are investigated before taking the investigational drug and after 6 and 12 weeks of medication. Participants with abnormal laboratory test results should be followed up. Additionally, total cholesterol, HDL cholesterol, LDL cholesterol, triglyceride, homocysteine, T3, free T4, and thyroid stimulating hormone (TSH) levels are investigated at baseline.

After visit 1 (baseline), the investigators monitor status of medication, adverse events, and concomitant medications via phone calls once a week until the next visit. After the end of the medication at visit 3 (12 weeks), the investigators monitor adverse events and concomitant medications via phone call every two weeks until the final visit.

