### Trial status

Recruitment of participants is currently in progress. Eight subjects were enrolled on Aug. 25, 2023.

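### The creatinine exclusion is printed as more than 10% of the upper limit of normal, a level that normal values exceed; the likely limit of 1.1 × ULN is stated nowhere

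*Protocol article*

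**What the plan says.** In the Protocol article, under Exclusion criteria, one item removes candidates with "Clinically significant abnormalities in blood chemistry tests". A bracket then gives two numerical limits: "AST/ALT: more than 2 times the upper limit of normal" and "serum creatinine: more than 10% of the upper limit of normal".

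The same list has one other renal item, "Patients with heart or kidney disease requiring acute treatment", which carries no laboratory value.

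Creatinine appears in two other places, each time only as a test to be done. The notes to Table 1 give "Laboratory test (basic): AST, ALT, glucose, BUN, creatinine, Na, K, Cl, LDH, CPK". The section Safety assessments and monitoring includes it in the panel taken before dosing and after 6 and 12 weeks, and adds: "Participants with abnormal laboratory test results should be followed up". Neither place gives a limit.

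**The concern.** A percentage of a limit is a fraction of it, so the printed words set the cut-off at one tenth of the ULN. Values between that point and the ULN are not raised, and a criterion meant to catch clinically significant abnormalities cannot be defined by them. The bracket therefore contradicts the phrase it is meant to explain.

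This is an eligibility and safety threshold for people over 65, and the only numerical renal limit in the article. Followed as printed, it would exclude candidates with normal kidney function. If it is not followed as printed, a reader cannot tell from the article which limit decides entry.

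**Working it through.** **Inputs from the article (Exclusion criteria)**

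- Creatinine limit as printed: 10% of the ULN.
- AST/ALT limit in the same bracket: 2 times the ULN.
- Reference range for creatinine: not given.

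**Step 1. Cut-offs as multiples of the ULN.** No outside figure is needed here.

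- Printed: 10% of ULN = 0.10 × ULN.
- Likely intended: ULN + 10% of ULN = 1.10 × ULN.
- AST/ALT: 2.0 × ULN.
- Ratio of likely intended to printed creatinine cut-off: 1.10 / 0.10 = 11.

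A limit for raised values has to lie at or above 1.0 × ULN. The AST/ALT limit does, and so does 1.10 × ULN. The printed creatinine limit does not.

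**Step 2. Cut-offs in mg/dL.** The ULN values are assumptions.

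| Assumed ULN | Printed, 0.10 × ULN | Likely intended, 1.10 × ULN |
|---|---|---|
| 0.9 | 0.09 | 0.99 |
| 1.0 | 0.10 | 1.10 |
| 1.2 | 0.12 | 1.32 |
| 1.3 | 0.13 | 1.43 |
| 1.4 | 0.14 | 1.54 |

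Take a ULN of 1.0 to 1.3 mg/dL and a lower limit of normal of 0.4 to 0.7 mg/dL, both assumed. The printed cut-off is then between 0.10 / 0.7 = 0.14 and 0.13 / 0.4 = 0.33 of the lower limit. It lies below the whole normal range, so every normal value would exclude.

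**Step 3. Share of candidates excluded.** Assume ULN = 1.2 mg/dL and a normal distribution of creatinine. The share excluded is 1 − Φ((cut-off − mean) / SD), with cut-off 0.12 (printed) or 1.32 (likely intended).

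| Assumed mean / SD (mg/dL) | Excluded at 0.12 | Excluded at 1.32 |
|---|---|---|
| 0.7 / 0.15 | 99.99% | 0.002% |
| 0.8 / 0.20 | 99.97% | 0.5% |
| 0.9 / 0.20 | 99.995% | 1.8% |
| 1.0 / 0.25 | 99.98% | 10.0% |

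These shares are illustrative. They show that the literal rule could not be run, and that the likely intended rule would exclude a modest share.

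**Step 4. Does anything else in the article settle the limit?** The other two mentions of creatinine have no threshold, and the other renal exclusion is qualitative. The Trial status section reports "Eight subjects were enrolled on Aug. 25, 2023". That shows the literal rule is not in use, since almost nobody could pass it, but not which limit is in use.

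**The case against.** The strongest reply is that this is a slip of one word that the context repairs. The bracket explains clinically significant abnormalities and stands next to a multiple of the ULN for liver enzymes, so a limit for raised values is plainly meant. Replacing *of* by *above* gives 1.1 × ULN, and no rival reading has been put forward. The enrolments confirm that the literal rule is not applied. Renal safety does not hang on this line alone either: acute kidney disease and edema are separate exclusions, the investigator may exclude on judgement, and creatinine is repeated during dosing. Finally, this is a journal article, and candidates are presumably screened from a full protocol that is not shown and may be worded correctly.

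Most of this is fair, and it limits the consequence. It does not make the printed line right. The intended limit remains an inference, and an exclusion threshold should be readable from the text. The point is not about detail left to another document: the article states a number, and the number is wrong.

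Two points bear on the remedy. Whether the full protocol has the same wording cannot be known from the article, so that should be settled first. And the screening items listed under Recruitment include no blood test, while the safety section places the first laboratory panel before dosing. The value to check is therefore best called the pre-dose creatinine.

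**Conclusion.** The concern holds. The creatinine exclusion is wrong as printed: it sets the limit at 0.10 × ULN, contradicts the criterion it belongs to, and is corrected nowhere else in the article. The likely intended limit is 1.10 × ULN, eleven times higher, but the article does not confirm it.

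The contradiction and the multiples 0.10, 1.10 and 2.0 follow from the text alone. The mg/dL values and the shares excluded rest on assumed reference limits and assumed distributions.

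The consequence is limited to eligibility and its reporting. Sample size, power and the primary analysis are unaffected, and nothing in the article shows that anyone was wrongly admitted or excluded. The line should be corrected because it is a stated safety threshold and the correction is nearly free. The finding concerns the article's text only.

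**What to change.** Compare the line with the full protocol and have the investigators confirm the limit. Then reword the criterion to read: serum creatinine more than 10% above the upper limit of normal (> 1.1 × ULN), or the confirmed limit if it differs. Writing it as a multiple of the ULN matches the AST/ALT limit and removes the ambiguity.

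Check the pre-dose creatinine of everyone already enrolled against the confirmed limit. This matters most if the full protocol carries the same wording.

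The cost is one line of text and a look at results that the visit schedule already provides for. At the reported status date that meant 8 participants, with 60 − 8 = 52 of the planned 60 still to be enrolled.

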#### Drop-out criteria

The investigators will discontinue the administration of the investigational drug and drop the subjects according to the dropout criteria. The subjects can also voluntarily withdraw from the trial at any time. The criteria for dropout are as follows:When a serious adverse event occurs or when the participant requests discontinuation of the study due to an adverse event.When a systemic disease is found that was not detected in the examination prior to the administration of the investigational drug.In case the participant or the participant’s legal representative requests to discontinue the study.The medication compliance is < 60% at visit 2 (6 weeks after taking the investigational drug).The medication compliance is < 80% at visit 3 (12 weeks after taking the investigational drug).When the participant withdraws consent to participate in the clinical trial.In case the participant is not tracked.In the case of taking drugs that may affect the study results without the investigators’ instruction or consent during the study period.In other cases where the investigators determine that it is inappropriate to proceed with the study.

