### Primary outcome

#### PSQI-K

The Pittsburgh Sleep Quality Index (PSQI) is a subjective evaluation tool for sleep quality that includes quantity, depth, and peace of sleep. Subjective sleep quality, sleep latency, sleep duration, sleep efficiency, sleep disturbance, sleep medication use, and daytime dysfunction are evaluated. Each domain has a minimum score of 0–3 points, and the total score of the seven subdomains ranges from 0 to 21 points [31]. The higher the total score, the higher the severity of the sleep disorder; if it exceeds 5 points, it is judged as a sleep disorder. In this study, the Korean version will be used that has been independently confirmed for validity and reliability [24].

The primary outcome is the difference between the treatment and placebo groups in terms of changes in the total PSQI-K score observed before taking the investigational drug, at the end of 12 weeks of medication, and after 12 weeks of 12-week medication.

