### Concomitant medication

It can be allowed at the discretion of the investigators if it does not fall under the prohibited drug category among the drugs taken at least 2 weeks before participating in the study. Drugs used for the transient treatment of other diseases should be administered in consultation with the investigators. For all other drugs, information (product name, purpose of administration, duration, dosage, etc.) are recorded in a case report form.

Drugs and non-pharmacological treatments that may improve insomnia or affect cognitive function are prohibited. If the participants have taken these drugs or received treatment during the medication period, the study will be discontinued.

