### Statistical analysis

All statistical analyses is a two-sided and the significance level is set at 5%. Statistical program SPSS (Ver 25.0 or more updated, IBM Corporation) will be used as the primary analysis tool. All participants randomized according to the intent-to-treat (ITT) analysis principle are considered as the Full Analysis Set (FAS). Participants who have completed taking investigational product for 12 weeks and completed up to the follow-up period (week 24) after 12 weeks are referred to as the protocol compliance analysis group, as per-protocol (PP).

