#### Efficacy analysis

Efficacy evaluation is based on the FAS analysis group, and efficacy is analyzed and presented with reference to the PP analysis group. For safety evaluation, the ITT analysis group is the main assay.

Analysis of primary efficacy endpoints.

Participants with PSQI-K scores before the study and at least once after consuming the investigational product are analyzed. Based on the baseline, the difference between the two groups in the total PSQI-K score change at weeks 12 and 24 is analyzed using repeated measures analysis of variance (RM ANOVA) and linear mixed model (LMM) methods.

2)Analysis of secondary endpoints.

The PSQI-K score change will be analyzed by a paired t-test within each group for changes at 12 and 24 weeks based on the baseline. The ISI-K score change will be analyzed using the paired t-test within each group and the independent t-test between the two groups at the 12-week dosing period and at 24 weeks based on the baseline. The SNSB-D and S-GDS score changes will be analyzed using the paired t-test within each group and the independent t-test between the two groups with respect to the score change at week 12, based on the baseline. The SF-36 score change will be analyzed using a paired t-test within each group and an independent t-test between the two groups at 12 and 24 weeks based on the baseline. Changes over time will be analyzed using the RM ANOVA and LMM methods. The estimated values of the mean difference between the groups, 95% confidence intervals, and p-values will be presented.

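### The drop-out and concomitant-medication rules disagree for weeks 12–24, and the wider one can cost the primary week-24 PSQI-K of a participant who starts an unapproved hypnotic

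*Protocol article*

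**What the plan says.** Drop-out criteria, lead sentence: "The investigators will discontinue the administration of the investigational drug and drop the subjects according to the dropout criteria". One listed criterion is "taking drugs that may affect the study results without the investigators’ instruction or consent during the study period".

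Concomitant medication: drug and non-drug treatments that may improve insomnia are prohibited, with no time limit on the prohibition itself. The consequence is limited in time: "If the participants have taken these drugs or received treatment during the medication period, the study will be discontinued".

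Safety assessments and monitoring: after week 12, "the investigators monitor adverse events and concomitant medications via phone call every two weeks until the final visit".

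The abstract states "The PSQI-K total score difference between the two groups at 12 and 24 weeks will be the primary outcome". The primary outcome section likewise takes the score before dosing, "at the end of 12 weeks of medication, and after 12 weeks of 12-week medication". Under Statistical analysis, the full analysis set is everyone randomised, on the intention-to-treat principle. Under Efficacy analysis, the primary endpoint is analysed in participants with a baseline and at least one later PSQI-K, and the change "is analyzed using repeated measures analysis of variance (RM ANOVA) and linear mixed model (LMM) methods".

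**The concern.** The study period runs to the week-24 visit, but dosing ends at week 12. In the second half there is no study drug left to stop, so the only effect the drop-out rule can have there is to end participation. The other rule attaches no such consequence after week 12. Two participants who do the same thing at week 16 could therefore be handled differently, depending on which section staff follow.

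What is at stake is half of the primary outcome. In an insomnia trial, a person who starts a hypnotic after treatment stops is probably sleeping badly. The week-24 scores lost this way are then unlikely to be a random subset. Removing people because of an event after randomisation also sits poorly with an analysis set of all randomised participants.

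**Working it through.** **1. The rules side by side, for a hypnotic started at week 16 without consent.**
- Drop-out criteria: the window is the study period, so the participant is dropped.
- Concomitant medication: the window is the medication period, so no consequence is stated.
- Detection: calls every two weeks over 12 weeks give 12/2 = 6 contacts, so the start would probably be noticed.
- Assessment after a drop: the article does not say that it continues. Loss of the week-24 score is inferred from the instruction to drop.

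**2. What the analysis does with such a participant.** Baseline and week-12 scores exist, so the participant stays in the primary analysis. The mixed model uses those scores, but it cannot see worsening after week 12. Repeated measures ANOVA in its usual form deletes the whole case.

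**3. Arithmetic fixed by the document (30 per arm).** One lost score is 1/30 = 3.3% of an arm. If it lies d points above the mean m of the other 29, the full mean is (29m + m + d)/30 = m + d/30. The observed arm mean is then too favourable by d/30; d = 5 gives 5/30 = 0.17 points.

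**4. Illustration; every input is assumed.** The true week-24 difference (KGT minus placebo) is −2.0 and the SD is 3.5. The standard error at 30 per arm is 3.5 × √(2/30) = 0.90. Starters lose their week-24 score.
- *Model A:* means at the three visits 12/10/10 (placebo) and 12/8/8 (KGT), equal correlation 0.3–0.7, odds of starting × 1.65 per week-24 point. Starts of 5–20% on placebo imply 2.2–10.8% on KGT. The mixed-model difference is −1.94 to −1.68, so 0.06 to 0.32 too small. With odds × 1.22 per point (correlation 0.5) the bias is under 0.1; with odds × 2.23 it reaches 0.36.
- *Model B:* means 12/10/11 and 12/8/9, correlations 0.5–0.6, score lost when the week-24 value plus noise exceeds a cut-off. With about 7–29% lost on placebo and 2–17% on KGT, the mixed-model difference has size 1.60 to 1.84, so 0.16 to 0.40 too small. Using observed week-24 scores only, it is 1.44 to 1.76.
- If starts are unrelated to the score, or follow worsening that is equal in both arms, the difference is not biased.

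The largest bias here is 0.40/0.90 = 0.44 of a standard error. Both models measure it against the week-24 score that would have been seen without a hypnotic.

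**5. What collecting the score would give.** A starter who attends week 24 supplies a score on the hypnotic. If the hypnotic lowers PSQI-K by b points, the difference between arms shrinks by b × (placebo starts − KGT starts). With Model A uptake and b assumed at 1–3, this runs from 1 × (0.05 − 0.022) = 0.03 to 3 × (0.20 − 0.108) = 0.28. PSQI-K also has a sleep-medication item scored 0–3, so starting a hypnotic can itself add up to 3 points and offset some or all of b.

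**The case against.** The strongest reply is that a consistent reading exists. The lead sentence ties dropping to stopping the study drug, which is possible only up to week 12. The specific rule on insomnia treatment names the medication period, and the later calls may simply record what is taken. On that reading, nobody is dropped in weeks 12–24. This is a fair reading, but it is not what the drop-out criterion says: its window is the study period, and nothing in the other section cancels it. The disagreement stands on either reading.

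Second, the article condenses a fuller protocol, which may keep dropped participants under assessment. This stands to the extent that the lost score is inferred. It does not remove the point, because the article states an instruction to drop and does not merely leave a detail out.

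Third, the reach is narrow: only drugs taken without the investigators' instruction or consent count, and contact is two-weekly. This stands.

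Fourth, the fix does not recover the score without a hypnotic, so it is partly a choice of estimand. This also stands. Collecting the score answers the treatment-policy question; the no-hypnotic question still needs assumptions.

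A reader might also infer that the rule inflates the result in favour of KGT, for example if sleep worsens once KGT is stopped and more KGT participants start hypnotics. Imposing 10% starts on placebo and 20% on KGT in Model A gives −2.18 to −2.34 against a true −2.0. That split is put in by hand, with no worsening modelled and with KGT scores still 2 points better. The documents give no support for it.

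**Conclusion.** The point holds in limited form. The two rules disagree for weeks 12–24, which is plain from the text. Read as written, the wider rule can end follow-up and so lose a primary week-24 PSQI-K for a reason probably related to the outcome, and the mixed model would correct this only in part. That consequence rests on two things: the literal window of the drop-out criterion, and the inference that a dropped participant is not assessed at week 24.

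The number affected and the size and direction of any bias cannot be determined from the document. Under the assumed inputs above, the bias is between nothing and about 0.4 points, less than half a standard error, and so probably modest. A reader might conclude that the primary result will be biased, or biased in a known direction; the documents support neither. The change is still worth making, because it is cheap and a score never taken cannot be analysed.

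**What to change.** Amend the drop-out criteria and the concomitant-medication section together, so that new drug or non-drug insomnia treatment after week 12 is recorded as a protocol deviation and does not end follow-up. Then:
- Collect week-24 PSQI-K, ISI-K and SF-36 on every randomised participant who has not withdrawn consent.
- Ask about non-drug treatment in the existing two-weekly calls, and report the number starting new treatment by arm.
- Make the week-24 comparison on all collected scores and label it a treatment-policy estimate.
- Beside it, show a sensitivity analysis that sets scores after new treatment to missing or to unfavourable values, and say that it rests on assumptions.

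The cost is wording in two sections, ethics approval of the change (which the Discussion already requires), one question in about six calls per participant, and one extra analysis. At the status date of 25 August 2023, 8 of 60 participants were enrolled. Recruitment was to start in May 2023, and 24 weeks from 1 May 2023 is 16 October 2023, so on those dates no week-24 visit had yet fallen due. The downside is slight extra work and possible dilution by the new treatment (0.03–0.28 points under the assumptions above), partly offset because PSQI-K scores sleep medication use.
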